# Metta-based group meditation and individual cognitive behavioral therapy (MeCBT) for chronic depression: study protocol for a randomized controlled trial

**DOI:** 10.1186/s13063-019-3815-4

**Published:** 2020-01-06

**Keywords:** Metta, Loving kindness meditation, Mindfulness, Cognitive behavioral therapy, Chronic depression, Persistent depressive disorder, Randomized controlled trial

## Abstract

**Background:**

Depression is a widespread disorder with severe impacts for individuals and society, especially in its chronic form. Current treatment approaches for persistent depression have focused primarily on reducing negative affect and have paid little attention to promoting positive affect. Previous studies have shown that metta meditation increases positive affect in chronically depressed patients. Results from previous trials provide evidence for the efficacy of a stand-alone metta meditation group treatment in combination with mindfulness-based approaches. Further research is needed to better understand the implementation of meditation practice into everyday life. Therefore, mindfulness and metta meditation in a group setting are combined with individual cognitive behavioral therapy (CBT) into a new, low-intensity, cost-effective treatment (“MeCBT”) for chronic depression.

**Methods/design:**

In this single-center, randomized, observer-blinded, parallel-group clinical trial we will test the efficacy of MeCBT in reducing depression compared to a wait-list control condition. Forty-eight participants in a balanced design will be allocated randomly to a treatment group or a wait-list control group. Metta-based group meditation will be offered in eight weekly sessions and one additional half-day retreat. Subsequent individual CBT will be conducted in eight fortnightly sessions. Outcome measures will be assessed at four time points: before intervention (T0); after group meditation (T1); after individual CBT (T2); and, in the treated group only, at 6-month follow-up (T3). Changes in depressive symptoms (clinician rating), assessed with the Quick Inventory of Depressive Symptoms (QIDS-C) are the primary outcome. We expect a significant decline of depressive symptoms at T2 compared to the wait-list control group. Secondary outcome measures include self-rated depression, mindfulness, benevolence, rumination, emotion regulation, social connectedness, social functioning, as well as behavioral and cognitive avoidance. We will explore changes at T1 and T2 in all these secondary outcome variables.

**Discussion:**

To our knowledge this is the first study to combine a group program focusing on Metta meditation with state-of-the art individual CBT specifically tailored to chronic depression. Implications for further refinement and examination of the treatment program are discussed.

**Trial registration:**

ISRCTN, ISRCTN97264476. Registered 29 March 2018 (applied on 14 December 2017)—retrospectively registered.

## Background

### Chronic depression: epidemiology and treatment approaches

Major depression is a widespread [1] disorder that involves significant psychosocial impairment [2]. If untreated, major depression frequently takes a recurrent or chronic course [3] and is associated with high economic burden [4]. A high proportion of the affected population suffers persistently from depressed mood, loss of interest, and other symptoms of depression, with some fluctuations but no distinct episodes [5]. The lifetime prevalence for chronic forms of depression is about 2–5% of the population in western countries [6, 7]. Chronic forms of depression are associated with significantly greater social and health-related impairment, increased comorbidity rates, and higher risk of suicide than less persistent forms of depression [8, 9]. Due to their homogeneous nature, the four subtypes of chronic depression (cf. Keller et al. [10]) were combined into one diagnosis in the Diagnostic and Statistical Manual of Mental Disorders, Fifth Edition (DSM-5): Persistent depressive disorder (PDD) [11].

Despite the heavy burden of long-lasting symptoms, chronic forms of depression are often not recognized and are not treated sufficiently and adequately according to national guidelines [12]. In general, success rates and treatment effects on patients with chronic depression are significantly lower than for non-chronic forms of depression [13]. The results of a network meta-analysis [14] that included pharmacotherapy, interpersonal psychotherapy (IPT), the Cognitive Behavioral Analysis System of Psychotherapy (CBASP), and combinations of pharmacotherapy and psychotherapy indicated effectiveness of medication, CBASP, and a combination of IPT and medication. A more recent meta-analysis [15] found moderate effect sizes of CBASP compared to treatment as usual (TAU) and IPT, small effect sizes against other psychological treatments, and no significant difference between CBASP and pharmacotherapy.

A possible alternative to psychotherapy approaches that focus on interpersonal processes is the combination of cognitive therapy with mindfulness-based meditation (MBCT) [16]. This has been shown to successfully reduce relapse in recurrent depression [17], with effects similar to pharmacological treatment [18]. Evidence for a possible efficacy of MBCT in chronic depression comes from non-randomized trials [19–22]. On the other hand, a recent randomized controlled study concluded that rather active, problem-focused interventions such as CBASP may be more effective than passive, self-related interventions such as MBCT [23]. One reason for the worse performance of MBCT could be the neglect of fostering positive emotions. However, the results of that study must be interpreted with caution as there were different outcomes for MBCT at the two sites of the study and MBCT was conducted in unusually small groups (four to six participants) compared to more traditional group sizes (eight to twelve participants).

### The role of positive affect in chronic depression

Research on the role of affect in depression implies that positive affect and negative affect should be regarded as distinct and independent factors [24]. Depression has been characterized as a state of high negative affect and low positive affect [25]. This implies that in the treatment of depression negative affect must be reduced while promoting positive affect. In chronic depression, experiential avoidance [26] and rumination are especially related to negative affect and have a strong impact on the persistence of depression [27]. Mindfulness meditation may be a good approach to reduce these mechanisms, as it fosters a de-identifying stance towards negative—but also positive—appraisal. However, there is still a need for patients to engage in activities that promote positive affect.

Fredrickson has formulated an empirically supported theory (*broaden and build-theory*) on why the increase of positive affect can be beneficial for individuals in the long term and how this can be promoted [28]. According to her theory, people who experience positive emotions *broaden* their attention and are better able to think flexibly, as opposed to negative emotions, where the attentional focus is often narrowed to threats. When positive emotions occur more often, and perception and thinking have been broadened, the possibility of *building* personal resources is created. Our approach extends current treatment approaches by focusing on correlates of positive affect on a more basic level, namely the attitude of benevolence and the readiness and ability to experience positive emotions.

### Metta meditation as a treatment for mental disorders

In Buddhism, “metta” (Pali; “benevolence”, “loving-kindness”, “friendliness”) is one of the four essential “attitudes”. It refers to a mental state of unselfish and unconditional kindness to all beings that one develops through meditation and cultivation in relations with others [29]. The main Western psychological and philosophical concept that refers to metta is benevolence, a value or attitude which refers to the motivation to do good. Unlike mindfulness-based meditation, metta meditation (or loving-kindness meditation) explicitly aims to promote positive emotional states and a positive attitude towards oneself and others [29]. By concentrating on individually derived repeated formulas, the motivation for positive activities, benevolent behavior, and the improvement of relations with other people is encouraged [30–32]. PDD is often associated with high self-criticism. A greater motivation to be more benevolent towards oneself may help to compensate for this deficit [33, 34]. In addition, the enhancement of positive affect may also contribute to the increase of resilience [35]. Furthermore, people suffering from PDD often have problems in their interpersonal relationships, such as a rather more submissive and hostile interpersonal style [36].

A recently published meta-analysis based on 22 controlled studies, most of which were conducted in the general population [37], showed that metta meditation not only reduces depression but also improves psychological well-being and interpersonal relationships. In two within-subjects single-arm pilot studies with patients suffering from PDD, our working group found evidence supporting the feasibility and safety of a group treatment that combined mindfulness and metta meditation with cognitive-behavioral techniques. In the first pilot study (*N* = 12) we found moderate to large effect sizes, based on depressive symptoms, after completion of treatment and at 3-month follow-up [38]. The patients reported significant changes in their emotion regulation strategies: suppression of negative feelings and rumination decreased, while acceptance increased. In a subsequent, also uncontrolled study (*N* = 12), a modified meditation program was evaluated [35]. After completion of treatment, large effects were achieved in the decrease in depressive symptoms. In addition, participants reported a significant increase in the ability to tolerate negative emotions. However, in both pilot studies the samples were small, control conditions were missing, and no longer term follow-up data were collected. Evaluations of qualitative interviews with patients after the treatment highlighted their difficulties in implementing the emotion-regulation techniques targeted in meditation into daily life activities. For example, a large proportion of patients with PDD show more experiential avoidance [39] and withdrawal from previous social life [40] compared to patients with recurrent depression. Therefore, we developed the intervention further to include subsequent individual sessions using cognitive-behavioral techniques to overcome problems in daily practice of meditation and to translate its goals, i.e., benevolence towards oneself and others, into concrete action.

### Overcoming avoidance as a potential mechanism in the treatment of chronic depression

Avoidance and suppression are dysfunctional strategies to regulate negative emotions [41] as they prevent recovery from depressive episodes [42]. In turn, improving an accepting attitude towards negative emotions is a significant predictor of successful treatment not only in MBCT [43] but also in CBT [44]. Interestingly, there is growing evidence that people with depression suppress not only negative and burdensome emotions but also positive emotions [45]. The avoidance of positive emotions may further reduce the motivation for engaging in activities that are positively reinforcing. A chronic history of depression was also linked to stronger tendencies to self-reported behavioral and cognitive/emotional avoidance than an episodic history of depression [46]. Thus, avoidance on a behavioral level as well as experiential avoidance may explain the maintenance and chronicity of depression. Meta-analyses showed that traditional CBT, and in particular behavioral activation [47], was superior to control conditions as well as medical treatment [48]. Thus, we chose to include CBT behavioral activation as well as cognitive restructuring as treatment components that may counteract avoidance tendencies.

### Childhood trauma and persistent chronic depression

A large body of research [49–52] indicates that childhood trauma or childhood adversity are risk factors for the development of PDD. Chronic depression was also significantly associated with a greater lifetime traumatic load and a higher prevalence of PTSD [7]. In a recent German study with *N* = 349 chronically depressed patients [53], 76% of the participants reported clinically relevant histories of traumatic experiences in childhood on at least one scale of the Childhood Trauma Questionnaire (CTQ). In this study the multiplicity of traumas in childhood was the strongest predictor of symptom severity, with emotional abuse and sexual abuse being the strongest predictors. This is consistent with findings that patients with a more persistent rather than episodic course of depression were significantly more likely to have suffered from childhood emotional abuse or neglect [39]. Differences in the individual history of childhood maltreatment in patients with PDD may influence the individual etiology and require special treatment elements. There is evidence that schema therapy may be effective in treating dysfunctional cognitive, emotional, and behavioral patterns due to early negative experiences [54]. Schema therapy is largely overlapping with CBT, including techniques of cognitive restructuring and behavioral activation, but adds interventions that focus on processing early maladaptive experiences and enhancement of healthy adult functioning. Therefore, to overcome stressful memories of adverse childhood experiences and the resulting dysfunctional schemas, we will also incorporate techniques of schema therapy as an option into our treatment.

### Rationale for the current trial

Based on the effects of metta meditation on positive motivation and affects, as well as the findings on deficits in chronic depression related to behavioral and emotional avoidance and early maladaptive schemas, we combined group metta meditation with individual CBT (including behavioral activation and schema therapy) to reduce depression as the principal aim of the treatment. As secondary outcomes of the study, we will assess variables that deliver information about the effects of essential strategies included in the treatment protocol:
Improving emotion regulation, increasing acceptance of negative thoughts, and reducing rumination by mindfulness meditationIncreasing benevolence and motivation to improve relations with other peopleOvercoming avoidance

The effects of the treatment on primary and secondary outcomes will be compared with changes in a wait-list control group in a single-center, randomized, observer-blinded, parallel-group study design.

### Hypotheses and research questions

The primary outcome measure in this trial is the difference in the severity of depressive symptoms between the two groups. The main research question is: Does the combination of group meditation and individual CBT lead to significantly greater reduction in depressive symptoms compared to a wait-list control condition after overall completion of treatment (at T2)?

The previous data suggest that, at least in the short term, a stabilization of mood improvements is possible by maintaining a regular meditation practice [38]. So far, little research has focused on the maintenance of therapy success of group meditation programs for PDD. Therefore, a secondary question is: Does the effect in the treated group appear to be maintained at the 6-month follow-up?

In addition to the primary outcome measure, further changes will be recorded regarding specific effect parameters related to the two treatment components (meditation and CBT). The aim is to enable an intermediate measurement to identify changes in the two phases of treatment. Therefore, another secondary question is: Compared to control group, are there any significant changes in patients’ mindfulness, benevolence, rumination, emotion regulation, social connectedness, social motivation, and behavioral and cognitive avoidance (a) after the group meditation program and (b) after completion of the overall treatment?

The design of this study does not allow us to test the separate effects of both components, group meditation and individual CBT, which would require a different design. Furthermore, we will not be able to conduct adequate mediation analyses as the statistical power would not be sufficient to do so. However, exploratory analyses will be conducted to examine whether pre-post changes in depression in the group meditation program are associated with changes in the subsequent individual treatment.

In addition, in line with research indicating that mindfulness-based meditation is associated with changes in emotion regulation, especially acceptance and revaluing [32], and the reduction of avoidance [55], we will explore whether changes in the variables “emotion regulation”, “behavioral avoidance”, and “cognitive avoidance” are associated with the primary outcome at post-treatment.

## Methods/design

### Design and setting

The present study is a single-center randomized controlled trial of a combination of group meditation and individual CBT versus a wait-list control condition. Participants in the control group will receive no treatment or treatment as usual (e.g., antidepressants), but no psychotherapy during the treatment of the experimental group. A wait list control group has been included to control for unspecific expectation effects and symptom fluctuations. We strive for equal group sizes. Outcome measures will be assessed at four time points: before intervention (T0); after group meditation (T1); after individual CBT (T2); and at 6-month follow-up (T3). T3 will be assessed only in the experimental group because the waitlist condition terminates after T2. The wait list control group will be offered the MeCBT program upon completion of the waiting period and the T2 measurement. Due to this design of the study, there will be no untreated control group at the T3 measurement after 52 weeks, and follow-up effects will thus be uncontrolled and modeled using data from intervention participants only. The study is conducted at the Department of Clinical Psychology and Psychotherapy at Goethe University Frankfurt. The study protocol adheres to the Standard Protocol Items: Recommendations for Interventional Trials (SPIRIT) checklist (Additional file 1). Figure 1 illustrates the study design.

**Fig. 1 Fig1:**
[figure not shown]
Flow diagram of the MeCBT study design. *CTQ* Childhood Trauma Questionnaire, *post-interv* post-intervention

### Participants

This trial will include patients who meet the following criteria.

Inclusion criteria:
Primary diagnosis of persistent depressive disorder according to DSM-5Aged 18–70 yearsNo current psychotherapeutic treatmentWritten consent to participate in the study

Exclusion criteria:
Αcute suicidalitySubstance abuse or dependence syndrome within the past 3 monthsPsychotic disorders or symptoms of bipolar disorderBorderline personality disorderOrganic mental disorder or serious physical illness

Concurrent psycho-pharmacological treatment is not an exclusion criterion. Patients continue to receive a pharmacological anti-depressant treatment if it is indicated and are encouraged to keep it constant. Changes in the type and dose of the medication are recorded and documented. The waiting period for the wait-list control group is comparable to the usual waiting time for patients in outpatient psychotherapy care in Germany.

Participants will be excluded from the study if:
The participant requests it (withdrawal of consent for participation)Further participation is associated with risks to the mental condition of the patientThe participant’s condition requires inpatient treatment

Participants may withdraw from the study for any reason at any time. The principal investigator also may withdraw participants from the study in order to protect their safety or if they are unwilling or unable to comply with required study procedures. If a patient’s condition requires further treatment after withdrawal from the study or after completion of the program, the patient will be offered psychotherapy at the Center for Psychotherapy of the Goethe University Frankfurt or alternatively will receive support to find appropriate counseling or health care.

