### Blinding

Diagnosticians collecting observer rated measures will be blind to participant assignment as timing of assessments will be the same for all participants of a cohort. Blinding of diagnosticians should be maintained under all circumstances. To ensure that blinding is maintained, participants will be asked not to indicate their allocation status to the diagnosticians. Due to the design of the study, intervention blinding of participants and research workers, who also act as therapists, is not possible. The principal investigator is not blinded as he also implements the group therapies and individual therapies. Statistical analyses will be conducted by the authors, who will not be blinded or independent.

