### Statistical analysis

The primary outcome measure is pre-post (i.e., T0–T2) changes on the QIDS-C. Intention-to-treat analyses will be employed in this trial. For the statistical analysis of the primary outcome we will use a three-factor mixed-design ANOVA with two two-level between-subjects factors (treatment and CTQ-based stratifier) and a two-level within-subjects factor (time, T0 and T2) in the model. For our primary outcome, the group difference at T2, we will use a model with an interaction of treatment by time. An additional analysis including T1 will be performed using planned contrasts to examine changes in depression after group and individual treatment. We will use a repeated measures MANOVA including a time by treatment interaction to assess the effects of secondary outcomes, which we assume to be moderately inter-correlated, followed by univariate repeated measures analyses.

An intended aim was to detect mechanisms of change, which requires a mediation analysis. However, mediation analyses using structural equation analyses and latent growth curve analyses require a larger sample size, more measurement occasions of potential mediators than given in our study, and the control of confounding variables between mediators and outcome [88]. Therefore, exploratory regression analyses using pre-post differences in primary and secondary outcome after the meditation group treatment and the individual treatment will be performed to detect possible candidates for mediation analyses within future studies. Missing data will be handled using multiple imputation procedures. Data collected about adverse events and serious adverse events will be summarized by type and frequency, and regression analyses will be conducted to explore relations between adverse events and treatment. For statistical analysis, the computer program SPSS® (Statistical Package for Social Sciences, version 25) will be used.

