### Plans to promote participant retention and complete follow-up

Once a participant is enrolled, the Trial Management Group will make every reasonable effort to keep in contact with the participant during the entire study period. If a participant expresses doubts about further participation, a personal dialogue will be offered to him or her to possibly find a way to continue participating in the study. In order to pursue participant retention during the entire study period, prior to data collection time points participants will be contacted and reminded of the upcoming data collection. No further measures (e.g., material or financial incentives) are planned to promote participant retention. If participants withdraw from treatment or are excluded from interventions due to risk or otherwise deviate from the study protocol, we will attempt to collect all planned outcome data. We will only refrain from collecting outcomes from those who withdraw fully from the entire trial.

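### Removal from the study for risk, inpatient treatment or non-compliance conflicts with the rule that outcomes are still sought, and T2 QIDS-C could go missing because of deterioration

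*Protocol article*

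**What the plan says.** In the protocol article, the Participants section introduces three grounds with "Participants will be excluded from the study if". They are withdrawal of consent, risk to the patient's mental condition from continuing, and a condition that needs inpatient treatment. The three share one list and one stated consequence. The same section adds that the principal investigator may "withdraw participants from the study in order to protect their safety or if they are unwilling or unable to comply with required study procedures". This power is discretionary, and its object is again the study, not the treatment.

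The section on participant retention and complete follow-up treats similar events differently. Having first named people who stop treatment of their own accord, it goes on: "excluded from interventions due to risk or otherwise deviate from the study protocol, we will attempt to collect all planned outcome data". It then limits the exception: "We will only refrain from collecting outcomes from those who withdraw fully from the entire trial". Inpatient treatment is not named there.

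The Statistical analysis section states "Intention-to-treat analyses will be employed in this trial" and "Missing data will be handled using multiple imputation procedures". The Blinding section notes that "The principal investigator is not blinded as he also implements the group therapies and individual therapies".

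**The concern.** A participant judged to be at risk is out of the study under one section and out of the interventions, but still assessed, under the other. Staff deciding whether to schedule the T2 interview for that person cannot tell from the text which applies. For inpatient treatment the only explicit statement is exclusion from the study.

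The primary outcome is change in QIDS-C from T0 to T2. Risk to mental condition and need for inpatient care are likely to go with worsening on that outcome, so missing scores that arise this way would depend on the value that is missing. Withdrawal for safety or non-compliance rests with a person who knows the allocation and delivers the therapy. The frequency of such removals could also differ by arm. The Adverse event monitoring section has therapists report weekly on suicidal ideation, and a wait-listed participant has no trial therapist before T2. The stake is bias in the between-arm comparison, not loss of power.

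**Working it through.** **1. The sections side by side**

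| Event | Participants section | Retention section |
|---|---|---|
| Withdrawal of consent | Out of the study | Full withdrawal ends collection |
| Risk to mental condition | Out of the study (mandatory) | Out of the interventions; outcomes sought |
| Need for inpatient treatment | Out of the study (mandatory) | Not named |
| Safety, at the investigator's discretion | May be withdrawn from the study | Risk: outcomes sought |
| Not complying with study procedures | May be withdrawn from the study | Protocol deviation: outcomes sought |

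Only the first row agrees without interpretation. Inpatient hospitalization would be recorded as a serious adverse event (Adverse event monitoring), but that record does not supply a T2 QIDS-C score.

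**2. Power is not the issue**

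Inputs from the Sample size section: f = 0.25, α = 0.01, power 0.80, r = 0.7, two groups, two time points, 25% dropout. With noncentrality λ = f²(N − 2)·2/(1 − r), power is 0.777 at N = 32 and 0.812 at N = 34, so the stated 34 is reproduced. Inflation for dropout: 34/0.75 = 45.3, rounded up to 46, as stated. With the planned 48, a 25% loss leaves 36, where power is 0.842. Loss within the planned rate is therefore affordable for power. The inflation does nothing about who is lost.

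**3. Possible size of the bias (assumed inputs)**

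The protocol gives no expected number of removals and no severity for them, so both are assumptions. If k of n participants in an arm are unobserved and lie on average c SD worse than the whole-arm mean, the mean of those who remain looks better by k·c/(n − k).

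- n = 24 per arm (48 in two equal groups), k = 2, c = 1.5: 2 × 1.5/22 = 0.136 SD.
- Same k, c = 1.0: 2 × 1.0/22 = 0.09 SD. With c = 2.0: 2 × 2.0/22 = 0.18 SD.
- If instead the worst 1, 2, 3 or 4 of 24 are lost and outcomes are normal, the shift is φ(z)/(1 − q), where q is the fraction lost and z the cut-off. This gives about 0.09, 0.17, 0.24 and 0.30 SD.

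These are complete-case shifts. With imputation, the shift would be close to the complete-case value if the observed data say nothing about the deterioration, and close to zero if they predict it fully.

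**4. Yardstick**

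The protocol states its effect only as f = 0.25. Let D be the between-arm difference in change, in units of the outcome SD. The variance of a change score is 2(1 − 0.7) = 0.6 SD², so λ = N·D²/(4 × 0.6). Taking λ = f²·N·2/(1 − r) = 0.0625 × 2/0.3 × N = 0.4167N gives D² = 0.4167 × 2.4 = 1.0, so D = 1.0 SD. Using N − 2 at N = 34 gives D = √(32/34) = 0.97. A shift of 0.136 SD is thus about 14% of the planned effect, if those removed had average baseline scores.

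**The case against.** The best reply is that the retention section is the only text that governs data collection, and it is explicit. It covers exclusion for risk and deviation from the protocol, and it confines non-collection to full withdrawal. The Participants section never says that assessments stop. On this reading the two sections are compatible, and the first merely uses loose words. This carries weight. A reader might infer that the plan does lose its worst outcomes; the documents do not establish that, and the loss follows only if the Participants section is applied literally.

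Other stronger readings also fail:

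- A reader might infer that intention-to-treat is abandoned. A missing T2 score does not remove a participant from the analysis set, since multiple imputation is planned. The imputation model is not shown and may use T0, T1 and self-rated depression.
- A reader might infer that non-compliers are removed automatically, or that only treated participants can be removed this way. The text says the investigator may withdraw them, and the ground is study procedures, which include assessments in both arms.
- A reader might set the 0.14 SD against a conventional 0.5 SD effect and call it more than a quarter. The protocol states no 0.5 SD effect; its f corresponds to about 1.0 SD under the formula above.

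What remains is that risk and inpatient treatment sit in the same list as withdrawal of consent, that inpatient treatment is unaddressed in the retention section, and that nothing says whether removal under the Participants section counts as full withdrawal.

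**Conclusion.** The conflict is real and should be resolved; it is more than a missing detail. If the Participants section is followed as written, T2 QIDS-C can be missing for reasons related to deterioration. Imputation that assumes missing-at-random may not correct this, particularly when the worsening comes after the last observed score. The bias favours MeCBT if the removals fall in the treated arm and works against it if they fall in the wait-list arm. Equal removals of similar severity in both arms would largely cancel. The illustrative size is 0.14 SD in one arm's complete-case mean, about 14% of the planned effect. It rests on an assumed 2 of 24 removed at 1.5 SD worse and is not a prediction. If the retention section is followed for every such case, including inpatient treatment, this source of missing data is largely avoided.

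**What to change.** Reconcile the Participants section with the retention section and leave the clinical criteria as they are. Distinguish two states: discontinuing the intervention (or, for controls, the waiting condition) and withdrawing from outcome assessment. For risk, inpatient treatment and non-compliance, state that the scheduled assessments are still sought: T1 and T2 in both arms, and T3 in the treated arm only, in line with Design and setting. State that outcome collection ends only when the participant withdraws consent to it. The discretionary non-compliance ground need not be deleted if it is assigned to the first state. Confirm that all randomised participants stay in the primary analysis, as the intention-to-treat statement already implies.

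The cost is a few sentences, plus some extra effort to assess people who have stopped treatment. Sample size and the primary model are unaffected.
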